## Abstract

**Background:**

Since the introduction of antiretroviral therapy (ART), the incidence of HIV-associated dementia has drastically fallen. Despite using ART, people living with HIV continue to experience less severe but limiting forms of HIV-associated neurocognitive disorder (HAND). People living with HIV who are on ART and experiencing symptoms of HAND may benefit from aerobic exercise.

**Objective:**

This protocol describes a randomized controlled trial designed to determine the effects of a 12-week aerobic exercise program on HAND in Southeastern Nigeria.

**Methods:**

At least 68 patients diagnosed with HAND will be randomly placed into either an aerobic exercise group or control group. Patients in the aerobic exercise group will perform a moderate intensity workout on a stationary bicycle ergometer, 3 times a week for 12 weeks. We will measure the primary outcomes including neurocognitive performance, prevalence of HAND, viral load, and CD4 count. We will evaluate postexercise neurocognitive performance using reliable neuropsychological tests relevant to people living with HIV, in line with the Frascati criteria. We will assess secondary outcomes such as quality of life, activity limitation, and social participation using the World Health Organization Quality of Life (WHOQOL)-Brief, and the Oxford Participation and Activities questionnaire. We will use exploratory statistics to test the data for normality and homogeneity. We will analyze the effect of the exercise program on HAND using relative risk (RR) and absolute risk reduction (number needed to treat). Analysis of covariance will be run to estimate the effect of exercise on quality of life and activity and participation level.

**Results:**

This funded trial was approved by the Institutional Review Board in May 2020. The protocol was approved on June 15, 2020. Enrollment commenced in January 2021 and was completed in May 2021. Over 60% of the participants were recruited at the time of first submission to JMIR Mental Health. Data curation is still ongoing; hence, data analysis is yet to be executed. Study outcomes are expected to be published in March 2022.

**Conclusions:**

This is a protocol for a randomized controlled trial that aims to evaluate the effect of a 12-week aerobic exercise program on HAND in Southeastern Nigeria.

**Trial Registration:**

Pan African Clinical Trials Registry PACTR202009483415745; https://tinyurl.com/2p97zpu9

**International Registered Report Identifier (IRRID):**

PRR1-10.2196/29230

## Introduction

### Background

HIV-associated neurocognitive disorder (HAND) is a common neurological complication reported among people living with HIV [1]. Before antiretroviral therapy (ART) was introduced in 1996, HIV-associated dementia was a progressive disorder leading to death within 6 months [2]. Since the introduction of ART, the mean survival rate following HIV-associated dementia has increased, and milder forms of HAND have become more prevalent [1,3-5]. Globally, approximately 50% of people living with HIV are affected by HAND, with rates varying across countries [6-8]. In resource-constrained African settings, the burden of HAND ranges from 14% to 88.3% [1,9,10] in contrast with 19% to 52% in resource-limited countries [11,12]. In sub-Saharan Africa, HAND affects between 18.8% and 88.3% of people living with HIV, with a pooled prevalence of 53% [13]. In Nigeria, the prevalence of HAND fluctuates with ART use and lies between 21.5% and 71.7% [1,14,15]. People living with HIV who have HAND often present with cognitive impairment as well as behavioral and motor abnormalities such as memory loss, impulsiveness, irritability, visuospatial difficulty, dyscalculia, and difficulty with concentration and attention [2,3]. Impaired cognitive ability impacts quality of life (QoL) and treatment adherence [16]. People with HAND may also progress from being asymptomatic to being severely impaired [17,18]. People with HAND generally have limited functional capacity resulting in low productivity, job loss, poverty, poor academic performance, reduced QoL, and poor treatment adherence [19,20].

Global efforts directed at eradicating HAND [20] include early intensification of ART [21] and use of intranasal insulin [22], psychostimulants [23], and adjunctive therapies [21,24]. According to current guidelines, ART should start as soon an individual is diagnosed with HIV with a cluster of differentiation-4 (CD4) count ≤500 cells/mm^3^ [25]. Timely ART initiation has led to a marked decline in the incidence of HIV-associated dementia. Although severe forms of HAND have become less common, people living with HIV continue to experience less severe but limiting forms of HAND despite ART use. The increasing incidence of HAND may be due to early HIV entry into the central nervous system, limited permeability of ART through the blood-brain barrier (BBB), reduced ART efficacy, increased drug resistance, virologic failure, adverse effects, and neurotoxicity [26-29].

A recent scoping review revealed limited rehabilitative treatment options for HAND [30]. Rehabilitation may include psychocognitive training [31] and physical exercise [32]. Psychocognitive exercises involving pen-and-paper or computerized cognitive programs are based mainly on restoring cognitive function [28,33]. These interventions often include cognitive training, cognitive stimulation, and cognitive rehabilitation using different tasks [28]. Examples include Captain’s log [34], Smart-Brain [35], and InSight [36]. In contrast, physical exercise interventions are compensatory and have been shown to slow down the progression of cognitive disorder in aging HIV-seronegative individuals [31,37-39]. Currently, few exercise interventions and treatment guidelines exist for rehabilitating HAND except for evidence-informed recommendations reported by O’Brien et al [40]. Although physical exercise may slow the decline in cognitive functioning among people living with HIV, research-generated evidence remains inconclusive due to heterogeneity in study designs and use of low-intensity exercises [32,41,42]. A recent systematic review revealed that the effect of structured exercise interventions on cognitive performance of individuals with HAND has not been investigated [43]. In HIV-negative individuals, long-term and intense aerobic exercise improves BBB permeability, enhances synaptic plasticity, improves neurotrophin secretion, and regulates neuroinflammation [15,44,45] and thus may benefit people with HAND. This study therefore aims to determine the effect of a 12-week aerobic exercise program on HAND. This protocol describes procedures that will be implemented to determine the effect of a 12-week aerobic exercise program on HAND. The data will provide supporting evidence about the suitability of aerobic exercise as a complementary therapy for mitigating neurocognitive disorder among people living with HIV. The outcomes will also provide evidence to strengthen the advocacy for including aerobic exercise in the management of people living with HIV experiencing neurocognitive disorder.

### Objectives

The specific objectives of this study are to determine the effect of a 12-week aerobic exercise program on the severity of HAND symptoms, determine the effect of a 12-week aerobic exercise program on CD4 count in individuals with HAND, determine the effect of a 12-week aerobic exercise program on plasma viral load in individuals with HAND, determine the effect of a 12-week aerobic exercise program on functional activity and social participation of individuals with HAND, and determine the effect of a 12-week aerobic exercise program on QoL of individuals with HAND.

### Trial Design

This is a parallel randomized controlled trial employing a restricted assignment scheme, where participants were allocated in a 1:1 ratio. The intervention is aerobic exercise, and the comparator is a no-treatment control group. All assessors will be blinded regarding participant identification of both the experimental and control groups.

## Methods

### Study Setting

This study is taking place at the Exercise Immunology Clinic of the Department of Physiotherapy, University of Nigeria Teaching Hospitals (UNTH) Ituku-Ozalla, Nigeria, and the University of Nigeria Enugu Campus (UNEC). A preliminary study revealed that approximately 50% of the prospective participants that visited the UNTH ART clinic were from Enugu Metropolis. The second site, UNEC, was chosen as a more centralized location for participants who resided in Enugu Metropolis and nearby environs. Participants were purposively selected to participate. To ensure consistency, the intervention team, which is comprised of 2 qualified physiotherapists and 2 trained research assistants, was trained by the principal investigator.

We identified prospective participants during a pilot study. Prospective participants, who lived in the Enugu metropolis and surrounds, were invited by text message to attend the ART clinic. Only participants able to travel to the study site with ease were invited to participate. Participants were randomly assigned to the intervention or control group. First, a sequence of random numbers was generated using Random Restricted Software 2.0. An independent person assigned the random numbers to either the intervention or control group by placing the generated numbers into A4, opaque, sealed envelopes, with only C or E written on an inconspicuous area of the envelope. Envelopes with C are control and E are exercise. The outcome assessors (the principal investigator and clinical psychologist) enrolled participants into the study, without knowing group assignments. Outcome assessors, including the principal investigator, neurologist and clinical psychologist, and data analyst, were also blinded while conducting neurological assessments. Care physicians were asked not to suggest any form of aerobic exercise to the patients throughout the study period. Trained physiotherapists conducted the treatment. Finally, the data were coded (C for control group and B for experimental group) so that the biostatistician will not know which group is experimental or control.

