### Sample Size

An estimated sample size of 68 (34 in each group) will have 90% power to detect a difference in means of 13.4 (the difference between a Group 1 mean, µ_1_, of 56 and a Group 2 mean, µ_2_, of 42.6) assuming that the common SD is 16.67 using a 2-group *t* test with a 5% 2-sided significance level.

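### Allocation concealment is not secured as described: the arm's own initial is written on the sealed envelope

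*Protocol article*

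**What the plan says.** The Trial Design section describes a parallel randomised trial "employing a restricted assignment scheme, where participants were allocated in a 1:1 ratio", with assessors blinded to group. Study Setting gives the mechanism. First, "a sequence of random numbers was generated using Random Restricted Software 2.0". Then "An independent person assigned the random numbers to either the intervention or control group", using "A4, opaque, sealed envelopes, with only C or E written on an inconspicuous area of the envelope". The meaning of the letters follows at once: "Envelopes with C are control and E are exercise". The next sentence states the property that this is meant to deliver: "The outcome assessors (the principal investigator and clinical psychologist) enrolled participants into the study, without knowing group assignments".

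Three other places bear on the remedy.
- **Results:** enrolment ended in May 2021 and the data have not been analysed.
- **Statistical Methods:** the groups are compared by a two-way repeated-measures analysis of variance. Confounders, neurocognitive scores among them, go into analysis of covariance where appropriate.
- **Neuropsychological Screening:** the overall neurocognitive score is reserved for covariate analysis should the need arise. The Abstract assigns analysis of covariance to quality of life and to activity and participation.

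**The concern.** An opaque sealed envelope conceals allocation only if the allocation is what it hides. Here the sealed content is a random number, and the arm appears on the envelope as its own initial. Protection comes from the position of the mark, not from the seal.

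Two safeguards depend on this.

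- **Selection at enrolment.** Candidates had been identified beforehand in a pilot study, the comparator is no treatment, and eligibility includes a judgement of readiness to exercise. An enroller who knew the next arm could, knowingly or not, let that colour who was entered and when.
- **Blinded assessment.** The principal investigator and the clinical psychologist both enrolled participants and assessed outcomes. A letter seen at enrolment would stay known at the later neurocognitive tests, which the assessor administers and scores.

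Every between-group comparison in the trial relies on the first safeguard, and the neurocognitive outcomes rely on the second as well.

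**Working it through.** This is a question of procedure, so the main check sets the statements of Study Setting side by side.

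1. **What is sealed?** The generated random numbers.
2. **What is on the envelope?** Only C or E, in an unobtrusive place.
3. **Is the letter a neutral code?** No. C stands for control and E for exercise, and each is the initial of its arm.
4. **Inside or outside?** The text does not use either word. A mark inside a sealed opaque envelope would not need an unobtrusive place, so outside is the natural reading.
5. **Does the mechanism deliver the claim?** The claim is that the assessors "enrolled participants into the study, without knowing group assignments". Taking 1 to 4 together, it holds only if they never saw the envelopes or never noticed the letter. The article asserts the result, but the marking it describes does not ensure it.
6. **Is this only condensed reporting?** No. The article gives the envelope's size, opacity, seal and marking. The difficulty lies in what it states about the marking.

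**The plan's design figure.** The Sample Size section says: "An estimated sample size of 68 (34 in each group) will have 90% power to detect a difference in means of 13.4", with SD 16.67 and a two-sided 5% level. The normal approximation gives n = 2 × (1.960 + 1.282)² × 16.67² / 13.4² ≈ 32.5, so 33 per group. The exact t test gives 33.5, so 34, with power 90.4% at 34 per group. The figure reproduces and is not in dispute.

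**Can a bias be computed?** Suppose k of the 34 participants in each arm were steered, in opposite directions, by d standard deviations. In an unadjusted comparison the spurious difference would be

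bias = 2 × (k/34) × d × 16.67.

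The document gives 34 and 16.67 but neither k nor d. With k = 0 the bias is 0. With k = 3 and d = 1, both assumed:
- bias = 2 × (3/34) × 16.67 = 2.94 points, and 2.94 / 13.4 = 22% of the target difference;
- SE = 16.67 × √(2/34) = 4.04, so the shift is 2.94 / 4.04 = 0.73 SE;
- the two-sided type I error is P(|Z + 0.73| > 1.96) ≈ 11%.

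Nothing in the article favours either pair of inputs, so the formula shows what the bias depends on and gives no estimate of it.

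**The case against.** The strongest reply has four parts.

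- **The article says that enrollers were unaware, and an independent person prepared the envelopes.** This stands as far as it goes. The article does not show that anyone read a letter or that the enrolling staff held the envelopes. Custody and opening may be set out in the full protocol, and their absence from an article is no fault. What remains is the marking itself, which is stated.
- **Each envelope might have held a list of numbers for one arm, so that the letter revealed no individual's allocation.** The text does not say so, and there would then be little reason to hide the letter. If this was the procedure, a sentence would settle the matter.
- **Baseline is already in the analysis.** This is partly right. The repeated-measures model includes the baseline visit, and analysis of covariance with neurocognitive scores is foreseen. But the group comparison in that model is not conditional on baseline. Its group main effect averages the baseline in, and its group-by-time term works on change, which is open to regression to the mean if people were chosen on an observed score. Covariate use of the overall score is left optional.
- **The harm is speculative.** Its size is, and no number should be attached to it.

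A reader might go further and infer that concealment was actually broken, that the enrolling staff hand-picked participants for an arm, or that type I error is about 11%. The document supports none of these. It reports no breach. It says that participants were purposively selected without saying by whom, and selection before allocation does not by itself unbalance the arms. The 11% rests on arbitrary inputs and an unadjusted comparison.

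**Conclusion.** The concern holds as a mismatch between a stated procedure and a stated property: with the arm's initial on the envelope, the mechanism does not secure the concealment that the article claims. It rests on one inference, that the letter was on the outside, which is the natural reading but not an explicit statement. Whether anything went wrong depends on who saw the envelopes, which the article does not say. If enrolling staff saw them, both selection and blinded assessment are in question. The direction and size of any bias cannot be derived from the document. The point still merits action because concealment underlies every comparison between the arms and the analysis can still be settled before results are known.

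**What to change.** Relabelling is no longer possible for this trial, so the remedy lies in reporting and analysis.

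1. State where the letter was, what could be seen without opening the envelope, and who held and opened the envelopes.
2. Qualify the statement that enrollers did not know assignments. If the letter was visible to them, report this as a limitation for both allocation and assessor blinding.
3. Before the analysis is run, make the comparison adjusted for the baseline value of each outcome (analysis of covariance) primary, in place of the repeated-measures analysis of variance with optional covariates. The baseline assessments have already been made. For presence of HAND, which every participant has at entry, the baseline overall neurocognitive score would have to serve as the covariate.
4. In any future trial with envelopes, put only a sequential number outside, seal the arm inside, and open the envelope after consent and baseline testing.

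Comparing the generated sequence with the order of enrolment would not settle the matter: someone who reads the next letter and delays or brings forward a candidate leaves the sequence intact.

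The cost is some wording, possibly a candid limitation, and a small documented change to the analysis plan. Adjustment removes steering on measured baseline scores. It does not remove steering on motivation or other unmeasured traits, and it does nothing for unblinded assessment.

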### Eligibility Criteria

We included patients if they met the following criteria: diagnosed with HAND and physically inactive (sedentary, <2 hours of exercise per week; ready to exercise upon assessment, not engaged in regular exercise for approximately 3 months before the study). Patients were excluded if they were older than 65 years; had uncontrolled hypertension (blood pressure [BP] ˃140/90 mm Hg), deafness, severe eye impairment, physical disability, history of traumatic brain injury, psychiatric illness, recent focal neurological deficit, active depression, alcohol or substance abuse, musculoskeletal injury, or acute illness capable of hampering exercise performance; pregnancy; or had angina pectoralis and/or shortness of breath at rest or during exercise. We excluded participants on cognition-enhancing drugs such as eugeroics, attention deficit/hyperactive disorder medications, and nootropic supplements.

### Informed Consent

Informed written consent was obtained from each participant before enrollment in the study, provided they had the capacity to give consent.

In this study, the control group receives no treatment. The efficacy of aerobic exercise in HAND rehabilitation has rarely been investigated; therefore, we are comparing aerobic exercise to no exercise, before comparing to other forms of exercise or therapy.

### Exercise Testing

Exercise testing is conducted using the Young Men Christian Association (YMCA) bicycle ergometer protocol at baseline and after a 12-week exercise program [46,47]. The YMCA protocol uses 2 to 4 stages of continuous exercise lasting 3 minutes, during which 2 heart rate (HR)-power output data points (steady-state HR) between 110 bpm and 150 bpm are needed. The test is designed to raise the participant’s steady-state HR to between 110 bpm and 150 bpm and 70% HR reserve or 85% of the age-predicted maximum HR (HRmax) for at least 2 consecutive stages. Using the Life-Fitness Cycle Ergometer (95Ci, Franklin Park, IL), the first 3-minute workload is set between 150 kg·m·min^-1^ and 300 kg·m·min^-1^ (25-50 watts). The speed is set at 50 rpm. HR is measured within the last minute of each stage. If an HR >110 bpm is obtained in the first 3 minutes, then only one additional 3-minute stage is performed by increasing the workload to 450 kg·m·min^-1^ (75 watts). If the second-stage HR is <110 bpm, the 3-minute third or fourth stage is performed at an additional workload of 150 kg·m·min^-1^ up to 750 kg·m·min^-1^ (125 watts), in order to obtain 2 HRs between 110 bpm and 150 bpm. At the end of the test, a 3-minute recovery period (cool down) at zero resistance is administered. HR is measured during the last minute of each stage. The 2 steady-state HRs are plotted against the respective workload on the YMCA graph sheet. The line generated from the plotted points is then extrapolated to the age-predicted HRmax, and a perpendicular line is dropped to the x axis to estimate the work rate (VO_2max_) that would have been achieved if the individual had worked to maximum capacity [46-48]. At the end of exercise testing, the participants are asked to return to the Physiotherapy department within 2 days to 3 days to commence the intervention.

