### Study Outcomes

The primary outcomes include neurocognitive performance, prevalence of HAND, viral load, and CD4 count. The secondary outcomes include maximum oxygen uptake (VO_2_), QoL, activity limitation, and participation restriction. Potential confounding variables include age, sex, level of education, vaccination, history of virologic failure, level of ART adherence, exercise adherence, ART regimen, ovulation status, history of recent vaccination, and seasonality. These variables will be measured at baseline, after 12 weeks, and 3 months after the intervention. Their change will be measured over time. Aggregation parameters will include proportion, mean, or median depending on how the data are distributed.

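### The cycle test has two upper heart-rate bounds, 150 bpm and a percentage of capacity, with no rule for which governs; its stage rules use only the first, so older participants may be tested above the second.

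*Protocol article*

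**What the plan says.** Exercise Testing describes a submaximal bicycle test at baseline and after the 12-week programme. Heart rate is bounded in several places in that section:

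- Points for the graph: "2 heart rate (HR)-power output data points (steady-state HR) between 110 bpm and 150 bpm are needed".
- Aim of the test: to bring "steady-state HR to between 110 bpm and 150 bpm and 70% HR reserve or 85% of the age-predicted maximum HR (HRmax) for at least 2" stages in a row.
- After the first stage: "If an HR >110 bpm is obtained in the first 3 minutes, then only one additional 3-minute stage is performed", at 75 W. The rule has no upper heart-rate check.
- Later stages: load is added, up to 125 W, "in order to obtain 2 HRs between 110 bpm and 150 bpm".
- Estimation: "The line generated from the plotted points is then extrapolated to the age-predicted HRmax", and the corresponding work rate is read off.

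The percentage appears only in the statement of aim. The HRmax equation is not given.

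On who is tested, Eligibility Criteria says "Patients were excluded if they were older than 65 years" and gives no lower age. Participant Timeline has every participant tested before the intervention. Study Outcomes says "The secondary outcomes include maximum oxygen uptake (VO_2_), QoL, activity limitation, and participation restriction".

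**The concern.** A fixed bound in beats per minute and a bound that falls with age can coincide at only one age. The statement of aim joins them with one connective and does not say whether the percentage is a ceiling, a level to be reached or an alternative. A tester who follows the stage rules literally never applies it.

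Two things are at stake. The first is the conduct of a test given to sedentary people aged up to 65: the article states a percentage bound that its own stage rules do not enforce. The criteria for discontinuing or modifying treatment are written for the aerobic exercise intervention, so they do not clearly cover the test. The second is standardisation. VO2max is estimated from a line through two points, and if testers differ in the ceiling they apply, measurement error is added to a secondary outcome.

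**Working it through.** The article computes no figure on this point, so there is nothing to reproduce. The check is direct arithmetic.

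**Inputs from the article:** band 110-150 bpm; 70% of HR reserve; 85% of age-predicted HRmax (all Exercise Testing); maximum age 65 (Eligibility Criteria).

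**Assumptions, because the article gives no values:** HRmax = 220 - age, or 208 - 0.7 x age; resting heart rate 60-90 bpm; lower age 18 where a share of the age range is quoted.

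**Formulas.** The 85% bound is 0.85 x HRmax. The reserve bound is rest + 0.70 x (HRmax - rest).

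**Where each bound equals 150 bpm**

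- 85% of HRmax: HRmax = 150/0.85 = 176.5. Age = 220 - 176.5 = 43.5, or (208 - 176.5)/0.7 = 45.0.
- 70% of reserve: HRmax = rest + (150 - rest)/0.70. At rest 60 this is 188.6, giving age 31.4 or 27.8. At rest 90 it is 175.7, giving age 44.3 or 46.1.

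Above the crossing age, 150 bpm exceeds the percentage bound. Below it, 150 bpm is the lower of the two.

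**Bounds by age (bpm)**

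| Equation | Age | HRmax | 85% HRmax | 70% reserve (rest 60 to 90) | 150 bpm as % HRmax |
|---|---|---|---|---|---|
| 220 - age | 30 | 190 | 161.5 | 151.0-160.0 | 78.9 |
| | 50 | 170 | 144.5 | 137.0-146.0 | 88.2 |
| | 60 | 160 | 136.0 | 130.0-139.0 | 93.8 |
| | 65 | 155 | 131.8 | 126.5-135.5 | 96.8 |
| 208 - 0.7 x age | 30 | 187 | 158.9 | 148.9-157.9 | 80.2 |
| | 50 | 173 | 147.0 | 139.1-148.1 | 86.7 |
| | 60 | 166 | 141.1 | 134.2-143.2 | 90.4 |
| | 65 | 162.5 | 138.1 | 131.8-140.8 | 92.3 |

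**Excess at age 65.** With 220 - age: 150 - 131.8 = 18.2 bpm over the 85% bound, and 150 - 135.5 = 14.5 to 150 - 126.5 = 23.5 bpm over the reserve bound. With 208 - 0.7 x age: 11.9 bpm, and 9.2 to 18.2 bpm. Overall this is about 9 to 24 bpm.

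**Share of ages 18-65 above the crossing age.** For 85% of HRmax: (65 - 43.5)/47 = 46%, or (65 - 45.0)/47 = 42% (the second from the unrounded crossing age). For 70% of reserve: from (65 - 46.1)/47 = 40% to (65 - 27.8)/47 = 79%.

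**The two percentages against each other.** They are equal only when 0.85 x HRmax = 0.30 x rest + 0.70 x HRmax, that is, when resting rate is half of HRmax. The percentage bound is therefore itself two different numbers for most people.

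**The case against.** **The sentence can be read as a joint cap.** Two ceilings joined by a conjunction can both apply, so the lower one governs and no older participant goes above the percentage. This reading is available, so overshoot is not certain. It does not repair the text, because no stage or point-selection rule applies the percentage.

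**The extent is easily overstated.** A reader might infer that the bounds conflict across most of the eligible ages. That treats the percentage as a ceiling for older participants and as a level to be reached for younger ones. Read consistently as a ceiling, there is no conflict below the crossing age, because 150 bpm is simply tighter. The share above it (42-46% for 85% of HRmax, 40-79% for reserve) depends on an equation, resting rates and a lower age that the article does not fix.

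**VO2max need not be affected.** A reader might also infer that VO2max rests on inconsistent points or that the arm comparison is biased. The plotting band is the same for everyone at both visits, allocation is randomised, and on a truly linear relation any two steady-state points give the same line. Nothing in the article shows testers changing ceilings. This stands: the effect is conditional, and mainly noise.

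**The test is safeguarded, and the article is condensed.** Stages do not aim for 150 bpm, load is capped at 125 W, participants are screened, and qualified physiotherapists do the testing. Termination rules may sit in a fuller document. These points lower the likelihood of a high heart rate. They do not settle which of two printed bounds governs, which is a conflict in stated text and not an omission.

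**Conclusion.** The point holds as an unresolved contradiction within Exercise Testing. Two upper bounds are stated, neither is given precedence, and the operative rules use one of them. Read as caps, they conflict above about age 44 to 45 for 85% of HRmax, and above an age between about 28 and 46 for 70% of reserve. At age 65, 150 bpm is 92-97% of predicted HRmax and about 9-24 bpm above the percentage bounds. These figures rest on the two assumed HRmax equations and on resting rates of 60-90 bpm.

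The rules as written permit testing above the stated percentage; they do not require it, and the article does not show that it happened. The consequence for VO2max is possible extra noise in a secondary outcome. No view is taken here on which bound is right.

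**What to change.** - **Text.** The clinical team should reconcile the statements in Exercise Testing into one upper limit and state the HRmax equation, which any percentage bound and the extrapolation both need. Limit and equation should be applied identically in both arms and at both visits, for ending the test and for choosing plotted points. The ceiling should not change between a participant's baseline test and post-test, since that would create the mismatch the change is meant to prevent.
- **Tests already done.** Enrolment is reported as complete and analysis as not yet run. Keep every participant in the intention-to-treat analysis of VO2max. Report, by arm and visit, how many plotted heart rates exceed each stated bound, naming the HRmax equation used.
- **Sensitivity analysis, if wanted.** Base it on a flag fixed at baseline, such as age or baseline test heart rate. Do not drop tests by post-test heart rate: training can change it, so exclusion could select differently by arm.

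The cost is an edit to the testing procedure and one tabulation from recorded heart rates and age, with resting heart rate for the reserve bound. No participant is lost from the main analysis. A baseline-flag sensitivity analysis would be smaller and would mostly set aside older participants, so its result should be read in that light.
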